### Study procedure

#### Recruitment and sample size

The recommended sample size for logistic regression analysis is a minimum of 5 outcome events per predictor variable (EPV) [29]. The maximum number of variables to be analysed in this study is 15 giving a minimum sample size of 150. Based on expected admissions to the treating institution over the recruitment period, it is expected that this will provide an estimated recruitment pool of 300 eligible participants and sample size of approximately 250 participants. This proposed sample size allows for variation in EVP, missing data and participants lost to follow-up.

Patients undergoing lumbar spinal surgery will be identified from the surgical lists. All eligible patients will be provided with an information pack containing a participant information statement, consent form, withdrawal of consent form and baseline outcome measures. The research physiotherapist will contact potential participants during the week prior to surgery to confirm eligibility and respond to any questions. Written consent will be obtained from all participants. Consent forms and baseline outcome measures will be collected from participants following admission to hospital. Demographic data and information about the surgical procedure will be collected from the participant and patient records during admission.

Following surgery, all participants will be fitted with an activPAL3 accelerometer (PAL technologies) to be worn for the first seven post-operative days, commencing the morning after the day of surgery. As per the manufacturer instructions, the accelerometer will be fixed to the upper thigh using a waterproof transparent Tegaderm dressing. This can then remain in place for the seven-day monitoring period, with a daily review to check for discomfort or irritation. This method of fixing the accelerometer to the thigh eliminates the need for participants to remove and apply the monitoring device for showering and sleeping, it does not require participants to wear a waist band or belt that would sit across the site of the lumbar surgery.

Where participants are discharged during the seven-day monitoring period they will be provided with information regarding the use and removal of the accelerometer, and a reply paid envelope to return the accelerometer to the researcher.

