#### Independent (predictor) variable

The predictor variable to be used in data analysis will be the total time spent walking (recorded as total time performing stepping activity) over the first seven post-operative days. This data will be recorded using an activPAL3 accelerometer and downloaded using software provided by PALtechnologies. The activPAL3 accelerometers provide a user-friendly measure of posture and walking with robust evidence for validity and sufficient reproducibility for this study [24–26]. As the activPAL3 accelerometer is worn on the thigh, the accuracy of the monitor is not reliant on arm swing and is not expected to vary if participants are using a gait aid.

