#### Independent (confounding) variables

Data will be collected for variables where there is either evidence to suggest they influence outcome following lumbar spinal surgery, or there is or strong theoretical rational for their inclusion. This will include age, gender, current smoking status [14, 15], obesity [14, 18], diabetes [14, 16, 17], depression [19, 20], duration of pain/symptoms [35], neurological deficit [14], anxiety, pre-operative activity, pre-operative mobility, surgical procedure, multi-level surgery, and pre-operative function.

Depression will be assessed using the Patient Health Questionnaire Depression Scale (PHQ-9), using a cut off score of ≥10 [36]. The PHQ-9 is a short, valid and reliable measure of depression, and has been recommended for use within the chronic back pain population [37]. Anxiety will be scored using the Generalised Anxiety Disorder 7-item Scale (GAD-7), using a cut off score of ≥10 [38]. The GAD-7 is a brief, seven question scale used to screen for, and assess the severity of anxiety. It has been validated in the general population [38]. Neurological deficit will be assessed by asking the participant if he/she is aware of any changes to the sensation or strength in their affected lower limb. This level of information is deemed appropriate for this study, as any sensory or motor deficit that the participant is unaware of is unlikely to have an impact on functional ability. Pre-operative activity will be assessed using the International Physical Activity Questionnaire Short Form (IPAQ-SF) [39, 40]. The IPAQ-SF is a brief, reliable seven item questionnaire that requires participants to report on physical activity undertaken over the previous seven day period [39, 40]. Physical activity is categorised into low, moderate and high activity levels. As it is expected that the majority of participants will report either low or moderate activity levels, the two categories of low and moderate/high activity levels will be used for data analysis. Baseline ODQ score will be used as a measure of pre-operative function. Pre-operative mobility will be categorised based on the response to Section 4 (Walking) on the ODQ. Participants will be categorised as having limited mobility if they score 3 or more - unable to walk more than 500 m, require a walking aid, or are confined to bed.

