#### Relationship between time spent walking and outcome

Multivariable logistic regression analysis will be used to investigate the relationship between the time spent walking in the first week after surgery and outcome at six months using SPSS software. The dependent variable in the logistic regression model will be the change in score on the ODQ, SF-36 (PCS), NRPS (back) and NRPS (leg) between baseline and six months. The change in scores on the ODQ, SF-36 (PCS) and NRPS will be dichotomised based on the threshold required to demonstrate a substantial clinical benefit.

Thresholds required to meet the minimum clinically important difference (MCID) have been identified for the ODQ, the SF-36 (PCS) and the NPRS [41] (Table 2). In addition, thresholds required to obtain a substantial clinical benefit (SCB), where patients report a major improvement in symptoms, have been defined for the ODQ, SF-36 (PCS) and NRPS in the lumbar fusion population [42] (Table 2). For the purpose of this study it has been assumed that SCB following lumbar fusion surgery provides a fair estimate of substantial clinical benefit following lumbar surgery in general. These thresholds allow the change in scores to be categorised as minimal improvement (below MCID threshold), moderate improvement (above MCID threshold, below SCB threshold) and substantial improvement (SCB threshold or greater).

**Table 2 Tab2:** MCID and SCB thresholds

Outcome measurement tool	MCID (points change)	SCB (points change)
ODQ	10	18.8
SF-36 (PCS)	4.9	6.2
NPRS (back)	2	2.5
NRPS (leg)	2	2.5

As all participants in this study are undergoing surgery with the aim of improving pain and physical function, it expected that the majority of participants in this study will report an improvement in scores above the MCID threshold. Therefore the SCB threshold will be used to analyse the impact of walking time on outcome (minimal/moderate improvement compared to substantial improvement). For each of the four dependent variables a multivariable logistic regression model will be generated comparing participant outcome relative to the SCB threshold.

With the exception of pre-operative function and surgical procedure, all confounding variables will be dichotomised (Table 3).

**Table 3 Tab3:** List of independent variables and classification for statistical analysis

	Classification				
1. Post-operative activity	Time spent walking (minutes)				
2. Age	1. < 65 years	2. ≥ 65 years			
3. Gender	1. Male	2. Female			

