4. Current smoking status	1. Non-smoker	2. Smoker			
5. Obesity	1. BMI < 30	2. BMI ≥ 30			
6. Diabetes	1. Not diabetic	2. Diabetic			
7. Depression	1. PHQ-9 < 10	2. PHQ-9 ≥ 10			
8. Anxiety	1. GAD-7 < 10	2. GAD-7 ≥ 10			
9. Duration of pain/symptoms	1. < median (months)	2. ≥ median (months)			
10. Neurological deficit	1. No deficit	2. Neurological deficit			
11. Pre-operative activity	1. IPAQ-SF - Mod/high	2. IPAQ-SF - low			
12. Pre-operative mobility	1. ODQ (section 4) < 3	2. ODQ (section 4) ≥ 3			
13. Surgical procedure	1. Decompression	2. Disc surgery	3. Fusion		
14. Multi-level surgery	1. Single level surgery	2. Multi-level surgery			
15. Preoperative function (ODQ%)	1. 0–20	2. 21–40	3. 41–60	4. 61–80	5. 81–100

Bivariate analyses will be carried out to assess the association between each confounding variable and each outcome measure. The variables that have an independent association with outcome will be included in the final regression model. Analysis of correlation between the independent variables will be carried out to assess for multicollinearity. Where variables are highly correlated, either the more relevant variable or the variable with the more complete data set will be retained in the final regression model [43].

Missing independent variable data will be managed based on the quantity of missing data per participant and per variable. In the case of missing or incomplete accelerometry data, participants will be removed from analysis where three or more days of recordings are missing. In the case of one to two days of missing data, the time spent walking each day will be estimated based on the mean daily walking time of the total sample population. Comparisons will be made between the characteristics of participants with and without missing data to ensure minimisation of bias [43]. The underlying assumptions of the model will be assessed using the SPSS software “goodness of fit” testing.

Bivariate analysis will be used to examine the association between post-operative walking time, and both patient satisfaction and post-operative complications as reported at six months.

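### Confounders enter each final model only if they pass a bivariate screen against that outcome, so confounders already chosen on evidence or theory can be dropped and the walking odds ratio keeps residual confounding

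*Protocol article*

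**What the plan says.** The section on independent (confounding) variables gives the basis for the candidate list: "Data will be collected for variables where there is either evidence to suggest they influence outcome following lumbar spinal surgery", or for which there is a strong theoretical reason. Table 3 numbers walking time as variable 1 and 14 confounders as variables 2 to 15.

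Under Recruitment and sample size the full list is used to size the study: "The maximum number of variables to be analysed in this study is 15 giving a minimum sample size of 150". About 250 participants are expected.

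The model-building text after Table 3 then adds a filter. "Bivariate analyses will be carried out to assess the association between each confounding variable and each outcome measure". Next: "The variables that have an independent association with outcome will be included in the final regression model". No entry threshold is given and no confounder is forced in. A second reduction deals with collinearity, where "either the more relevant variable or the variable with the more complete data set will be retained in the final regression model". The process is repeated by outcome: "For each of the four dependent variables a multivariable logistic regression model will be generated comparing participant outcome relative to the SCB threshold".

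**The concern.** Four features of the rule do not fit the study's purpose.

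- The test and the wording disagree. A bivariate analysis shows a crude association, and whether it is independent of the other variables is what such an analysis cannot tell.
- Confounding depends on links with both outcome and exposure. The rule uses the outcome link alone. Links with walking time are examined only as a separate research question and play no part in selection.
- A confounder with a moderate effect often fails a significance test at this sample size. Failing it is weak evidence that the variable can be left out, and the subject-matter case for including it had already been made.
- The screen runs separately for each outcome, so the same exposure will probably be adjusted for different variables in the four models.

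At stake is the main result, the adjusted association between first-week walking and substantial improvement. The Discussion section intends to use it to judge whether raising activity should be a focus of rehabilitation. Patients in worse condition may both walk less and recover less, so omitted confounders could push the estimate towards a benefit of walking.

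**Working it through.** **The plan's own figure.** Minimum N = events per variable × variables ÷ event rate = 5 × 15 ÷ 0.5 = 150. This reproduces the stated 150 if half the participants reach the SCB threshold, a rate the article does not state. The 15 are walking time plus all 14 confounders, so the stated minimum assumes no screening.

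**Chance that a real confounder passes the screen.** Two-proportion power, with assumed confounder prevalence 30% and reference event rate 50%. An odds ratio of 1.5 moves 50% to 1.5 ÷ 2.5 = 60%.

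| Odds ratio | N | Pass at p<0.05 | Pass at p<0.20 |
|---|---|---|---|
| 1.5 | 250 | 0.30 | 0.57 |
| 1.5 | 150 | 0.20 | 0.44 |
| 2.0 | 250 | 0.69 | 0.88 |
| 2.0 | 150 | 0.47 | 0.73 |

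With four real confounders of odds ratio 1.5 at N=250, the chance of losing at least one is about 1 − 0.303⁴ = 0.99 at p<0.05 and 1 − 0.568⁴ = 0.90 at p<0.20. Simulation agrees (99% and 90%).

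**Different sets across outcomes.** If the four screens were independent, one such confounder would get the same decision in all four with probability 0.303⁴ + 0.697⁴ = 0.24 at p<0.05. The outcomes are correlated, so the true figure is higher. Even so, agreement on every confounder is unlikely.

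**Effect on the walking estimate.** Simulation with 14 binary covariates (30% prevalence), some of them real confounders of odds ratio 1.5 that also lower walking, about 50% events, no true walking effect, N=250, 2,000 trials per row. Each cell gives type I error and mean log odds ratio per SD of walking (truth 0).

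| Real confounders | Shift in walking, each | Screen p<0.05 | Screen p<0.20 | Full model |
|---|---|---|---|---|
| 2 | 0.5 SD | 4.8%, 0.04 | 4.1%, 0.01 | 5.2%, 0.00 |
| 4 | 0.3 SD | 6.4%, 0.05 | 5.1%, 0.02 | 5.3%, 0.00 |
| 4 | 0.5 SD | 7.0%, 0.07 | 4.6%, 0.03 | 5.2%, 0.00 |
| 6 | 0.5 SD | 13.4%, 0.11 | 7.2%, 0.05 | 7.4%, 0.00 |

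With eight confounders at N=200 (35% prevalence), two sets of runs at p<0.05 gave type I error of 10.6% and 11.7% for a 0.3 SD shift, and 18.1% and 17.7% for 0.5 SD. The biases were 0.11 and 0.17. The full model gave about 4% to 6%, with bias 0.00 to 0.01. At p<0.20 the screened type I error was 6.5% and 6.6%, and bias ranged from 0.04 to 0.08 over shifts of 0.2 to 0.5 SD.

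**Interval width.** In the eight-confounder runs the screened model's mean standard error (0.151 to 0.158) matched the empirical SD of its estimates (0.154). Under-coverage therefore comes from bias and not from width.

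**Size of the full model.** Table 3 holds walking time (1 slope), 12 two-level confounders (12), surgical procedure with three levels (2) and pre-operative function with five levels (4): 1 + 12 + 2 + 4 = 19 slopes. At 5 per slope that is 95 in the smaller outcome group: 95 ÷ 0.5 = 190 participants, 95 ÷ 0.4 = 238, 95 ÷ 0.3 = 317.

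**The case against.** The best defence is that the article is condensed and a separate plan may set a liberal threshold. That has force. At p<0.20 the type I excess largely goes, and the screened estimate even had lower root mean squared error than the full model in the eight-confounder runs (about 0.157 against 0.169 at a 0.2 SD shift, 0.180 against 0.196 at 0.5 SD). So screening does buy some precision. A threshold would not change the principle, however: selection would still rest on the outcome association alone, and some bias would remain.

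A second defence is that the aim is prediction. But the article calls these variables confounders and means to draw conclusions about whether to promote activity. That use needs a properly adjusted estimate.

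Several stronger readings are tempting and are not supported:

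- *The screen inflates false positives by a fixed amount.* The figures depend on the unstated threshold and on the number and strength of confounders. With two confounders there was no excess.
- *The confidence interval is too narrow.* The simulated standard errors do not show this.
- *The four results cannot be compared, or their adjustment sets must differ.* The outcomes are to be analysed individually and no comparison between them is planned. Different sets are likely, not certain.
- *The final model will be presented as if prespecified.* Nothing says so, and the selection is openly described.
- *The full model is already covered by the sample size.* This is true by variable count (15), but the model has 19 slopes.
- *Walking time itself could be screened out.* "The predictor variable to be used in data analysis will be the total time spent walking", and the screen is described for the confounders only. The collinearity rule, though, is worded for the independent variables generally and does not expressly protect walking time.

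**Conclusion.** The point stands as a weakness in a stated method, not as a missing detail. The rule cannot establish what its wording claims, takes no account of walking time, and can remove confounders that the article had already justified and counted. The consequence is residual confounding in the walking odds ratio.

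Its size is conditional. At p<0.05 the bias is about 0.05 to 0.17 on the log odds scale per SD of walking, with type I error of about 6% to 18%, against about 0 and 4% to 7% for the full model. At p<0.20 the bias is about 0.02 to 0.08 with little or no type I excess. These figures assume 200 to 250 analysed, 50% events, and four to eight confounders of odds ratio 1.5 that all act in the same direction. Fewer, weaker or opposing confounders would give less. The documents fix none of these inputs.

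**What to change.** Change the analysis wording as follows.

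1. Delete the bivariate screen as an inclusion rule. Keep the bivariate results as description.
2. In all four models, adjust walking time for the same prespecified core set of Table 3 confounders, whatever their bivariate results.
3. Add the outcome's own baseline score to the three non-ODQ models (PCS, back pain or leg pain). Table 3 contains only baseline ODQ, but Table 1 shows that the other scores are collected before surgery. The models then share a core and differ by one stated term.
4. Settle known overlaps, such as ODQ section 4 with the total ODQ score, before outcomes are seen. State that walking time is never dropped.

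The cost is slightly wider intervals and a larger model. Entering baseline ODQ as continuous saves three slopes: 19 − 3 = 16, which needs 16 × 5 = 80 in the smaller outcome group (160 participants at 50% events, 200 at 40%, 267 at 30%). With an added own baseline it is 17 slopes and 85 (170, 213, 284). About 250 analysed covers the 50% and 40% cases. If the smaller group is nearer 30%, or losses are heavy, Firth penalisation can be named in advance as the fallback. No new data or extra enrolment is needed.

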## Method

### Aims

This research will investigate the relationship between the time spent walking in the week following lumbar surgery, and recovery of physical function. The primary aim is to establish whether the amount of walking patients do in the week following lumbar spinal surgery predicts improvement in function at six months. The data collected will also be used to generate an activity profile to describe the overall patterns of activity in the first post-operative week, and to identify factors that may influence the amount of activity patients undertake.

The research questions are:Does the amount of time spent walking during the week after lumbar spinal surgery predict improvement in function at six months?What proportion of time do patients spend performing active tasks (standing and walking) compared to sedentary behaviour (sitting and lying) in the week following lumbar spinal surgery?Is the amount of time spent walking in the first post-operative week influenced by restricted pre or post operative physical function, post-operative pain or complications, or the need for supervision while walking?

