#### Six-month follow-up

At 6 months following surgery participants will be sent follow-up outcome measures, to be returned to the researchers by mail.

All participants will receive routine inpatient physiotherapy management. As part of routine management participants are encouraged to walk at least 3 times daily over a comfortable distance, increasing both the frequency and distance as able. An exercise program is also commenced within the first 3 days following surgery, and includes activation of deep core muscles in a supine position, exercises to gently increase range of motion including lumbar rotation and neural slides, and lower limb strengthening. A single researcher will conduct all participant communication, measurement, data collection and application of accelerometers.

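### Filling one or two missing accelerometer days from the whole-sample mean pulls affected weekly walking totals toward that mean; a minor-to-moderate flaw that is cheap to correct

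*Protocol article*

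**What the plan says.** The main exposure (Independent (predictor) variable) is the "total time spent walking (recorded as total time performing stepping activity) over the first seven post-operative days". Table 3 enters it in minutes, without categories.

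The missing-data paragraph after Table 3 sets two rules. First, "participants will be removed from analysis where three or more days of recordings are missing", so anyone whose total is filled has at least five recorded days. Second, where a participant lacks only one or two days, the plan is that "the time spent walking each day will be estimated based on the mean daily walking time of the total sample population".

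The same paragraph adds one safeguard: "Comparisons will be made between the characteristics of participants with and without missing data to ensure minimisation of bias". It describes no sensitivity analysis of the filled values.

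Two other places bear on the rule. Under Six-month follow-up, routine care encourages participants to walk several times a day, "increasing both the frequency and distance as able". Under Aims, the third research question treats differences between patients in walking time as real and worth explaining: "Is the amount of time spent walking in the first post-operative week influenced by restricted pre or post operative physical function".

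**The concern.** A participant with five or six recorded days has already shown how much he or she walks. The rule makes no use of this when filling the gap and gives a very low walker and a very high walker the same value. The error is therefore systematic: upward for low walkers, downward for high walkers.

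The wording does not say whether the mean is pooled over all seven days or taken for the missing day. If it is pooled, the rule also ignores any rise in walking during the week, which the routine advice is meant to produce.

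The weekly total is the exposure in all four logistic models and enters the bivariate analyses of satisfaction, complications and factors associated with walking. This is a stated analysis rule, not a detail left to a fuller document.

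**Working it through.** The plan gives no figure for the effect of this rule, and no standard deviation, day trend or rate of lost days. The algebra in steps 1 to 3 rests on the stated rule and the assumptions named; step 4 is simulation.

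**1. Pull toward the mean (flat day profile).** Let m be the sample mean per day, a the participant's own mean, and k the number of missing days (1 or 2). The filled total is (7 − k)a + km; the true total is 7a. The filled total's deviation from 7m is (7 − k)(a − m), against a true 7(a − m). The share kept is (7 − k)/7: 6/7 = 86% for one day and 5/7 = 71% for two.

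| Participant | True total | One day filled | Two days filled |
|---|---|---|---|
| a = 0.5m | 3.5m | 4.0m (+14.3%) | 4.5m (+28.6%) |
| a = 2m | 14m | 13m (−7.1%) | 12m (−14.3%) |

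**2. Post-operative day (pooled mean, assumed linear trend).** If walking triples from day 1 to day 7, the daily values relative to the mean run from 0.5 to 1.5 in steps of 1/6.
- Days 6 and 7 sum to 1.333 + 1.5 = 2.833 but are filled with 2. The error is −0.833/7 = −11.9% of the total.
- Days 1 and 2 sum to 0.5 + 0.667 = 1.167 but are filled with 2. The error is +11.9%.
- A doubling gives ±7.9% and a fourfold rise ±14.3%.

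**3. Effect on the main slope (approximation).** Let a fraction f lose two days at random, with a flat profile, no day-to-day variation and c = 5/7. Treating the slope as linear, filled slope / true slope = [(1 − f) + fc] / [(1 − f) + fc²].
- f = 5%: 0.9857/0.9755, or +1.0%
- f = 10%: 0.9714/0.9510, or +2.1%
- f = 20%: 0.9429/0.9020, or +4.5%
- f = 30%: 0.9143/0.8531, or +7.2%

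With one day lost (c = 6/7), the range from f = 5% to 30% is +0.6% to +4.0%. The slope is inflated, not attenuated: the exposure is compressed while the outcomes are unchanged.

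**4. Simulation (200,000 participants, log-normal person and day effects).** All variances and trends are assumed.
- Logistic slope, walking tripling over the week, days 6 and 7 lost at random: +0.8%, +1.9%, +4.2% and +6.8% for 5%, 10%, 20% and 30% affected. When low walkers lose days more often: +0.7% to +4.2%. Across all the settings tried, the range is about 0.5% to 8%.
- Weekly totals of affected participants, days 6 and 7 lost, day-7/day-1 ratio from 1 to 4, intraclass correlation 0.3 to 0.7: lowest fifth of walkers +9% to +33%, highest fifth −10% to −27%. The standard deviation of the filled totals is 0.58 to 0.75 of the true one.
- Day-specific sample mean, walking doubling, intraclass correlation 0.5, days 6 and 7 lost: the overall mean error is zero, but the lowest fifth is overstated by 35% (20% with the pooled mean) and the highest fifth understated by 15% (20% pooled).
- Own recorded days scaled by the sample's day profile: mean error zero overall, at most about 3% in either extreme fifth, and a slope within about 2% of the complete-data slope in the tripling scenario.
- The participant's own simple mean is not enough: with days 6 and 7 lost, its mean error is −11% if walking doubles and −20% if it rises fourfold.

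**The case against.** The strongest reply is that the primary estimate hardly moves. The number affected is unknown. Recruitment and sample size describes a waterproof dressing that stays on for showering and sleeping, with daily review, which should limit lost days, although participants discharged early look after the device at home. Sampling error is also larger than the bias. With 250 participants and an assumed 50% event share, the standard error of the log odds ratio per standard deviation of walking is roughly 1/√(250 × 0.25) = 0.126 before adjustment. An 8% shift in an assumed log odds ratio of 0.4 is 0.032, about a quarter of that. This objection stands, and it limits the severity.

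Three stronger readings are tempting, and the document does not support them.
- A reader might infer that the recorded days are thrown away. They stay in the total; they are only not used to fill the gap.
- A reader might infer that low walkers are misclassified. Walking time is analysed as continuous minutes, and no low-walker cut-off is defined.
- A reader might take the day-of-week-after-surgery error as certain. The wording can mean a day-specific mean, which would remove that error, and the protocol gives advice to increase walking but no measured trend. Ignoring the participant's own level remains a fault under either reading.

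The gain from scaling also depends on how steady people are. With log-scale standard deviations of 0.6 between and 0.35 within persons, the root mean squared error was 2.0 to 2.8 times smaller than under the plan's rule. With 0.4 and 0.6, it was only 1.1 to 1.6 times smaller.

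The planned comparison of participants with and without missing data may show selective loss, but it leaves the filled values as they are.

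**Conclusion.** The point holds as a minor-to-moderate flaw in how the main exposure is built. The pull toward the mean follows from the stated rule, and with a flat profile its size needs no further assumption: 14% or 7% for one missing day and 29% or 14% for two, at half and twice the sample mean. The further error of about ±12% for two lost days requires a pooled mean and an assumed tripling of walking.

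The main log odds ratio is inflated by about 0.5% to 8% if 5% to 30% of participants lose two days, under assumed variability. That does not invalidate the study. It is still an avoidable error, and it is largest in relative terms for the limited walkers whom the Discussion hopes to identify.

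**What to change.** Replace the rule for one or two missing days. Preferred: multiple imputation of daily walking time, with the participant's other recorded days, post-operative day, the model covariates and the six-month outcome as predictors. Leaving out the outcome would tend to weaken the association being estimated.

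Simpler alternative: filled total = own recorded total × (sample mean over all 7 days / sample mean over the days that participant recorded). Check: for a participant at half the mean with days 6 and 7 lost and walking tripling, the recorded total is 0.5 × (7 − 2.833)m = 2.083m, and 2.083m × 7/4.167 = 3.5m, the true total.

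The cost is revised wording and a few lines of code, with slightly more analysis work for multiple imputation and no new data. The simple scaling has one drawback: if day-to-day variation within a person is large, it can mildly attenuate the slope (up to about 4% under the assumptions tried). That is why multiple imputation is preferred.
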